# Effect of short-term compression therapy after thermal ablation for varicose veins: study protocol for a prospective, multicenter, non-inferiority, randomized controlled trial

**DOI:** 10.1186/s13063-023-07609-1

**Published:** 2023-10-12

**Keywords:** Varicose veins, Thermal ablation, Compression therapy, Targeted vein occlusion rate, Randomized controlled trial, Study protocol

## Abstract

**Background:**

For patients with varicose veins, the goal is to relieve pain and swelling, reduce the severity of edema, improve skin changes, and heal ulcers associated with venous disease. Compression therapy is the cornerstone of their management. Several studies have shown that wearing an elastic bandage for the first 24 h and then a compression stocking for a week can effectively reduce the pain after thermal ablation. However, in clinical practice, patient compliance with this treatment could be better, considering difficulties in pulling up and removing the compression stocking, tightness, and skin irritation because these must be worn for a prolonged period. A potential solution to battling these barriers is short-term compression therapy. Besides, the effect and necessity of wearing compression stockings after thermal ablation have been questioned. Based on current clinical experience and limited evidence, although some scholars have suggested that compression therapy may be an unnecessary adjunctive therapy after thermal ablation, there is still a great deal of uncertainty in the absence of compression therapy after thermal ablation compared to compression therapy. Therefore, we advocate further research to evaluate the clinical effect of short-term postoperative compression therapy. Furthermore, well-designed randomized controlled trials are needed.

**Methods:**

A prospective, multicenter, non-inferiority randomized controlled trial is designed to evaluate the non-inferiority of target vein occlusion rate at 3 months. Three hundred and sixty patients will be randomly assigned in a 1:1 ratio to one of the following treatments: (A) 3 M™ Coban™ elastic bandage for 48 h or (B) 3 M™ Coban™ elastic bandage for the first 24 h and then a class II compression full-length stocking (23–32 mm Hg) for 1 week. The two groups will be compared on several variables, including target vein occlusion rate at 3 months (primary outcome indicator), pain, quality of life, clinical severity of varicose veins, postoperative complications, time to return to regular work, and compliance.

**Discussion:**

Suppose the effect of the 3 M™ Coban™ elastic bandage for 48 h proves to be non-inferior to long-term compression therapy. In that case, this short-term treatment may contribute to a future update of clinical guidelines for compression therapy after thermal ablation of varicose veins, resulting in higher patient compliance and better postoperative quality of life.

**Trial registration:**

Clinical Trials NCT05840991. Registered on May 2023.

**Supplementary Information:**

The online version contains supplementary material available at 10.1186/s13063-023-07609-1.

## Introduction

### Background

*Varicose veins* are a disease/syndrome in which the subcutaneous veins of the lower extremities are dilated, prolonged, and tortuous, reaching at least 3 mm in diameter[1]. Varicose veins are present in 10–30% of the general population; this percentage increases with age [2]. The conventional treatment for varicose veins is high ligating/stripping (HL/S) of the great saphenous vein [3]. Since the 1990s, radiofrequency ablation (RFA), endovenous laser ablation (EVLA), and ultrasound-guided foam sclerotherapy (UGFS) have been widely used in the treatment of varicose veins [4]. Among them, RFA and EVLA have primarily replaced traditional surgery with shorter operative time, lower postoperative complication rates, and shorter recovery times [5–13]. Compression therapy is commonly used after invasive treatment of varicose veins in the lower extremities, a strategy inherited from post-surgical varicose vein care. It aims to maintain occlusion of the treated veins and prevent bruising and recanalization [14]. Elastic bandages and compression stockings are the most popular form of compression devices.

The American Venous Forum suggests starting with an elastic bandage a few days after the procedure, and the pressure should be over 20 mmHg [15]. Based on the experience of generations of clinicians and relevant evidence-based medical evidence, the National Institute of Health and Care Excellence recommends using compression (bandaging or hosiery) for no more than 7 days after interventional treatment for varicose veins [16]. Several studies have shown that wearing an elastic bandage for the first 24 h and then a compression stocking for a week can effectively reduce the pain after thermal ablation. Elderman [17] compared the difference in pain between those who wore elastic bandages for the first 24 h and then a class II compression stocking for 2 weeks and those who only used elastic bandages for 24 h. It was found that compression stocking was significant for pain relief during the first week postoperatively. Ye [18] also compared the above compression therapies and found that wearing compression stockings reduced the severity of pain during the first postoperative week in C2 varicose veins patients. However, there was no significant benefit after wearing the stockings for more than 1 week. Based on this, Bootun [19] compared the outcomes of patients treated with compression stockings for 1 week after an elastic bandage for the first 24 h with those who only wore an elastic bandage for 24 h. They found that patients in the compression stockings group had significantly lower pain scores than others at 2–5 days; it suggests that wearing compression stockings for a week after venous thermal ablation may be sufficient to relieve pain. However, poor patient compliance is a frequent problem in clinical practice with wearing compression stockings, with considerations related to difficulties in pulling up and removing the compression stockings, concerns with tightness, and skin irritation because these must be worn for a prolonged period [20]. In addition, subsequent clinical trials have questioned the necessity and effect of wearing compression stockings after thermal ablation. AYO [21], who evaluated whether wearing stockings for 1 week after endovenous thermal ablation could improve clinical outcomes in patients, showed that compression therapy had no significant effect on the outcome after thermal ablation in patients with non-ulcerated varicose veins. Pihlaja [22] found that patients without compression therapy after RFA had a 100% vein occlusion rate at 6 months compared to those wearing compression stockings for 2 weeks. The study results of Onwudike [23] also showed that the clinical effect of not wearing compression socks after thermal ablation was not worse than that of wearing compression socks for 2 weeks, which supported the conclusion that the extensive use of compression socks for compression therapy after thermal ablation had no clinical benefits for patients. Besides, a meta-analysis suggested that 48 h may be an ideal short-term compression therapy for patients with varicose veins treated with thermal ablation only [24].

Based on current clinical experience and limited evidence, although some scholars have suggested that compression therapy may be an unnecessary adjunctive therapy after thermal ablation, there is still a great deal of uncertainty in the absence of compression therapy after thermal ablation compared to compression therapy. Therefore, we advocate further research to evaluate the clinical effect of short-term postoperative compression therapy. In summary, the quality of current published studies must be improved due to the small sample size, lack of detailed data on compression therapy, and inconsistent findings. Moreover, most existing studies focus on postoperative pain, with less attention to the target vein occlusion rate; further well-structured randomized controlled trials are needed. In this study protocol, we propose to evaluate the non-inferiority of the target vein occlusion rate at 3 months. We expect to provide a basis for simplifying the compression therapy after thermal ablation.

### Objectives

The study’s primary objective is determining the target vein occlusion rate at 3 months, assessed with a Duplex ultrasound scan. Recanalization will be defined by a segment of the vein ≥ 5 cm. Secondary objectives are to compare the two treatment groups for pain scores at baseline, 1 week, and 3 months using a visual analog scale (VAS); quality of life scores at baseline, 1 week, and 3 months using the AVVQ (Aberdeen Varicose Vein Questionnaire); clinical change using the VCSS (Venous Clinical Severity Score) at baseline, 1 week, and 3 months; postoperative complications including edema, ecchymosis, paresthesia, skin burn/discoloration, phlebitis, hematoma, infection, deep vein thrombosis, and pulmonary embolism; time is taken to return to routine work; patient compliance with the intervention assessed with a questionnaire.

### Methods

The following information follows the SPIRIT reporting guidelines [25].

#### Study design

The study design is a prospective, multicenter, non-inferiority, randomized controlled trial.

#### Participants

This trial was conducted in patients with primary varicose great saphenous veins of lower extremities diagnosed in nine target hospitals from April 2023 to August 2023. All participants included in the trial signed an informed consent form.

#### Inclusion criteria

The inclusion criteria are aged 18 to 80, primary unilateral lower limb saphenous varicose veins; clinical grades C2 to C4; diameter of the main trunk of the saphenous vein in the thigh segment ≥ 2 mm to ≤ 15 mm; and agree to participate in this study and voluntarily sign the informed consent form.

#### Exclusion criteria

The exclusion criteria are known to have difficulty tolerating surgery; the main trunk of the saphenous vein is extremely twisted or tightly attached to the skin; previous history of ipsilateral varicose vein surgery in the lower extremity; combined deep vein thrombosis or previous deep vein thrombosis in the affected lower extremity; uncorrectable coagulation dysfunction or a significant blood abnormalities with significant bleeding tendency (platelets ≤ 30 × 10^9/L); ankle-brachial index (ABI) < 0.6 and/or absolute ankle pressure < 60 mmHg; known allergy to bandage or stocking used in the treatment; pregnancy or breastfeeding; involvement in other clinical trials; and other patients deemed unsuitable for this study by the investigator.

#### Randomize and blinding

Patients will be randomized (using a random number table generated by the Excel RANDOM function) to group A or B. A fixed data analyst will generate the table of random numbers via computer. The randomization scheme will be hidden from doctors and patients. Since the intervention in this trial could not blind the doctors and patients, only the data analyzers were blinded.

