#### Description of intervention

Before compression therapy, all patients will undergo a standard thermal ablation procedure (RFA, Medtronic Closure Fast or EVLA, Eufoton 1470 nm ring laser). Patients will be randomized to groups A or B. Patients randomized to group A will be asked to wear the 3 M™ Coban™ elastic bandage for 48 h after the surgery. Patients randomized to group B will be asked to wear the 3 M™ Coban™ elastic bandage for 24 h and then a class II compression full-length stockings (23–32 mmHg) day and night time for 1 week (Fig. 1). The surgeon will place the bandages on the patient's leg while still lying on the operating table after thermal ablation. By the way, implementing short-term or long-term compression therapy will not require alteration to usual care pathways (including the use of any medication) and these will continue for both trial arms.

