#### Primary outcome

The study’s primary outcome is the target vein occlusion rate at 3 months, assessed with a duplex ultrasound scan. Recanalization will be defined by a segment of the vein ≥ 5 cm.

Target vein occlusion rate = number of target venous closure cases in the group/total number of cases in the group.

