#### Follow-up

Patients will be followed up in the outpatient clinic at 1 week and 3 months. At the 1 week follow-up, patients will be asked to record pain scores with VAS, fill out a quality of life questionnaire (AVVQ), and will have their clinical scores assessed (VCSS). They will also be asked how soon they could return to regular work, postoperative complications, and compliance with the intervention. A venous Duplex scan will be held to determine the occlusion of the target vein. Follow-up at 3 months after thermal ablation will be the same as at 1 week follow-up.

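### As written, the 3-month duplex that decides the primary outcome is read without masking, for a reason that does not apply to its reader; the analyst blind is also left unprotected

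*Protocol article*

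**What the plan says.** The section Randomize and blinding makes three statements on who knows the allocation. On the list: "A fixed data analyst will generate the table of random numbers via computer". On concealment: "The randomization scheme will be hidden from doctors and patients". On blinding: "Since the intervention in this trial could not blind the doctors and patients, only the data analyzers were blinded".

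Under Primary outcome: "The study’s primary outcome is the target vein occlusion rate at 3 months, assessed with a duplex ultrasound scan". Recanalization is tied there to a vein segment of 5 cm or more. The Follow-up section describes the 1-week visit: pain, quality of life and severity scores, return to work, complications, compliance, and then "A venous Duplex scan will be held to determine the occlusion of the target vein". It makes the 3-month visit the same. The Baseline section gives each centre two permanent staff for data collection and follow-up, an investigator and a checker. No section says who performs or reads the scan.

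Under Description of intervention, group A's compression is short: "Patients randomized to group A will be asked to wear the 3 M™ Coban™ elastic bandage for 48 h after the surgery". Group B has the bandage for 24 h and then the stocking "day and night time for 1 week".

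**The concern.** There are two separate points, and the first matters more.

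**Reader of the primary outcome.** The reason given for limiting the blind concerns people who deliver or wear the compression. A person who scans the leg at 3 months need be neither. If that person knows the arm, the call on a borderline segment can follow expectation. In a non-inferiority trial a reader who expects no difference pushes the result towards success, and so does a reader who favours the shorter regimen; a reader who trusts stockings pushes the other way. Requiring success in both the intention-to-treat and the per-protocol sets gives no protection, because both sets use the same readings.

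**Analyst blind.** A data analyst makes the random table, the scheme is described as hidden from doctors and patients but not from analysts, and analysts are the only party declared blinded. Whoever makes the table can know the allocations. If that person also analyses the data, the one blind that the trial claims is lost.

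**Working it through.** **1. Does the stated reason cover the 3-month reader?** Group A: assigned compression ends at 48 h, that is day 2. Group B: 24 h of bandage plus 1 week of stocking, 1 + 7 = about day 8. Taking 3 months as about 90 days, the scan comes about 90 − 8 = 82 days after the last assigned compression in either arm. No assigned device should be on the leg, so the impossibility of blinding doctors and patients does not carry over to a separate reader. At 1 week it may, since group B may still be in stockings; the point is limited to the 3-month scan.

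**2. Is the reader masked as written?** The article says "only the data analyzers were blinded". The reader of the scan is not a data analyzer, so on the plain meaning of that sentence the reader is not blinded. The compliance question, asked at the same visit, tends to reveal the arm.

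**3. The plan's own sample size.** Inputs from Sample size and study duration: control rate 98%, margin 6 points, one-sided 2.5%, power 90%. With unpooled variance and no true difference:

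n = (1.960 + 1.2816)² × 2 × 0.98 × 0.02 / 0.06² = 114.4, rounded up to 115 per group, 230 in total. The stated figure reproduces.

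**4. How many readings decide the result?** 360 randomized 1:1 gives 180 per arm. The planned 20% drop-out leaves 180 × 0.8 = 144. Expected failures per arm are 144 × 0.02 = 2.9, about 3. Take 3 failures in B (3/144 = 2.08%).

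- *Score test*, z = (fA − fB − 0.06) / SE, where f is the observed failure proportion and SE uses maximum-likelihood rates restricted to a 6-point difference; non-inferior if z < −1.96.
  - 4 in A: restricted rates 7.26% and 1.26%, SE 0.02353, z = (0.00694 − 0.06)/0.02353 = −2.25. Passes.
  - 5 in A: restricted rates 7.34% and 1.34%, SE 0.02374, z = (0.01389 − 0.06)/0.02374 = −1.94. Fails.
- *Wald interval*, upper limit = (fA − fB) + 1.96 × √[fA(1 − fA)/n + fB(1 − fB)/n]; non-inferior if below 6 points.
  - 5 in A: 1.39 + 1.96 × 1.935 = 5.18 points. Passes.
  - 6 in A: 2.08 + 1.96 × 2.047 = 6.10 points. Fails.

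With all 180 per arm evaluable and still 3 failures in B:

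| Evaluable per arm | Test | Most failures in A that pass | Fewest that fail |
|---|---|---|---|
| 144 | Score | 4 | 5 |
| 144 | Wald | 5 | 6 |
| 180 | Score | 6 (z = −2.11) | 7 (z = −1.82) |
| 180 | Wald | 7 (upper 5.61) | 8 (upper 6.32) |

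The article's Statistical analysis section names no non-inferiority test, so both are shown. The Wald form uses the same unpooled variance that reproduces 115.

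**5. Illustration of one-directional misreading (assumed, not in the documents).** Let true occlusion be 92% in A, exactly at the margin, and 98% in B, and let a share s of A's open veins be called closed, so that the recorded rate in A is 0.92 + 0.08s. Chance of declaring non-inferiority, Wald interval, exact enumeration:

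| s | 144 per arm | 180 per arm |
|---|---|---|
| 0 | 3.5% | 4.0% |
| 10% | 6.8% | 8.1% |
| 20% | 12.3% | 15.5% |
| 30% | 21.2% | 27.4% |

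The excess over 2.5% at s = 0 comes from the Wald interval at rates near 1, not from misreading.

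**6. The analyst blind.** The list-maker is called a fixed data analyst and the blinded party the data analyzers. The text neither equates nor separates them.

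**The case against.** **The reader's status is inferred.** No section names who reads the duplex, and the key sentence is mainly about doctors and patients. This is a condensed article, and a full protocol is available on request that may describe masking. That is fair, but the article goes beyond silence: it says that only the analyzers were blinded. If readers were masked, that sentence is wrong and needs correcting.

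**The analyst blind may be intact.** A reader might infer that the list-maker and the analyzers are one person, so that the only blind is broken and the trial has no working blind at all. The documents do not support this. The two terms differ, and a single designated list-maker who takes no part in the analysis fits the wording. What stands is that no separation is stated.

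**The arithmetic shows no bias.** A reader might take the boundary counts to mean that one scan will reverse the trial. Any test on counts has such an edge. The counts show how little separates pass from fail when failures are rare; they say nothing on how often scans are misread or in which direction. The edge also moves with the test and the evaluable number. All of this stands, and the misreading shares in the working are assumptions.

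**Masking may not be easy everywhere.** The documents do not say whether the nine centres have a sonographer apart from the two follow-up staff, and marks on the leg are not discussed. It is an inference that masking is feasible, drawn from compression having ended weeks before.

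**Conclusion.** The point holds as a worthwhile improvement, not as a demonstrated flaw in the result. As written, the primary outcome is read without masking, and the reason given does not cover the 3-month reader. This rests on taking the word only at face value and on compression having ended by about day 8.

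As to size, with 3 failures in B the pass/fail edge in A lies between 4 and 5 (score) or 5 and 6 (Wald) at 144 per arm, and between 6 and 7 or 7 and 8 at 180. Against about 3 expected failures per arm, a handful of readings can settle the conclusion. That is sensitivity at the edge; no reader bias is documented or measured.

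The second point is smaller: the analyst blind is unprotected because the roles are not separated. The documents do not show that it has failed. The sample size is unaffected by either point.

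**What to change.** For the 3-month scans still to come:

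1. Have the duplex done and recorded by existing site staff who have no access to the allocation, before and apart from the compliance question.
2. Ask the patient not to disclose the regimen, and record any unmasking.
3. State in the protocol who reads the scan and whether that person is masked. If readers have been masked all along, one corrected sentence is enough.

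For the analysis: have the primary analysis run on coded arms until database lock, by an analyst other than the one who made the random table. Having someone else make the table is no longer possible, because the Trial status section puts the first enrolment on May 22, 2023 and the list is in use.

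The cost is an instruction to the sites, a reassigned analysis task, and some scheduling effort where one staff member now does both scan and interview. No extra scans or visits are needed. Patients will sometimes unmask the reader. Scans already done cannot be masked, and the report should say how many were read before the change.

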#### Description of intervention

Before compression therapy, all patients will undergo a standard thermal ablation procedure (RFA, Medtronic Closure Fast or EVLA, Eufoton 1470 nm ring laser). Patients will be randomized to groups A or B. Patients randomized to group A will be asked to wear the 3 M™ Coban™ elastic bandage for 48 h after the surgery. Patients randomized to group B will be asked to wear the 3 M™ Coban™ elastic bandage for 24 h and then a class II compression full-length stockings (23–32 mmHg) day and night time for 1 week (Fig. 1). The surgeon will place the bandages on the patient's leg while still lying on the operating table after thermal ablation. By the way, implementing short-term or long-term compression therapy will not require alteration to usual care pathways (including the use of any medication) and these will continue for both trial arms.

**Fig. 1 Fig1:**
[figure not shown]
Trial flowchart. VAS, visual analog scale; AVVQ, Aberdeen Varicose Vein Questionnaire; VCSS, Venous Clinical Severity Score

#### Primary outcome

The study’s primary outcome is the target vein occlusion rate at 3 months, assessed with a duplex ultrasound scan. Recanalization will be defined by a segment of the vein ≥ 5 cm.

Target vein occlusion rate = number of target venous closure cases in the group/total number of cases in the group.

#### Secondary outcomes

The secondary outcomes include the following:PainPatients will be asked to record pain scores with VAS, and the scale ranges from 0 (no pain) to 10 (worst pain imaginable) [26].Quality of lifePatients will be asked to fill out the AVVQ to measure the health status of varicose vein patients based on symptoms and impact on daily activities. A total score ranging from 0 to 35, with 35 being the worst quality of life [27].Venous clinical severityPatients will be asked to fill out the VCSS to evaluate the severity of the hallmarks of venous disease. The questionnaire consisted of ten questions, each of which was answered by 0 (none), 1 (mild), 2 (moderate), and 3 (severe)—a total score ranging from 0 to 30, with 30 being the worst quality of venous disease [28].Postoperative complicationsPostoperative complications include postoperative edema, ecchymosis, sensory abnormalities, skin burns/discoloration, phlebitis, hematoma, infection, deep vein thrombosis, and pulmonary embolism.Time to return to regular workThe investigator will use a uniform question to ask the patient how long it takes to return to regular work, life, or both (days), and then record.ComplianceCompliance refers to the extent to which patients follow compression therapy as recommended by their clinicians. Investigators will ask patients whether they have completed compression treatment as recommended by their doctors in the past week or 3 months. The answer to this question involves 1 (none), 2 (occasionally), 3 (mostly), and 4 (entirely). Those who still need to fully follow the study protocol for compression treatment should continue to be asked about their actual compression treatment and recorded.

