#### Statistical analysis

Continuous data will be compared by the Student *t*-test or Mann–Whitney *U* test for parametric and non-parametric data, as appropriate. Categorical data will be compared by the chi-square test or Fisher’s exact test, as appropriate. Considering the participants might crossover or be lost to follow-up, we will test non-inferiority using two analysis sets. One is the intention-to-treat set, considering all patients as randomized regardless of whether they received the randomized treatment, the other is the per-protocol set. We propose declaring short-term compression therapy non-inferior to long-term compression therapy, only if shown to be non-inferior using both the “intention-to-treat” and “per-protocol” analysis sets. *P* < 0.05 will be considered statistically significant, and all data will be analyzed using SAS 9.2 software.

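### The compliance item records completion rather than total wear, so extra compression in group A may be missed and kept in the per-protocol set

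*Protocol article*

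**What the plan says.** All references are to the protocol article.

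- **Regimens (Description of intervention).** Group A: "Patients randomized to group A will be asked to wear the 3 M™ Coban™ elastic bandage for 48 h after the surgery". Group B: "elastic bandage for 24 h and then a class II compression full-length stockings", the stocking being worn "day and night time for 1 week".
- **Compliance item (Secondary outcomes).** Patients are asked whether they completed compression as their doctors recommended, over the past week or 3 months. Answers run from 1 (none) to 4 (entirely). The question about actual wear follows for some patients only: "Those who still need to fully follow the study protocol for compression treatment should continue to be asked about their actual compression treatment and recorded".
- **Timing (Follow-up).** "Patients will be followed up in the outpatient clinic at 1 week and 3 months". At 1 week, "They will also be asked how soon they could return to regular work, postoperative complications, and compliance with the intervention". The 3-month visit repeats the same assessments.
- **Purpose (Data collection and confidentiality).** The compliance question is meant to show whether participants stop or deviate from the intervention.
- **Decision rule (Statistical analysis).** Crossover and loss to follow-up are anticipated. Short-term compression is declared non-inferior "only if shown to be non-inferior using both" the intention-to-treat and the per-protocol sets.

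**The concern.** In a non-inferiority trial the most dangerous deviation is the one that makes the arms alike. Here that is a group A patient who goes on using compression after 48 h. The article makes this plausible. The Background describes compression as common practice after these procedures and cites trials in which stockings eased pain in the first week. Doctors and patients are unblinded, and the analysis section itself expects some crossover.

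The item does not ask about that behaviour directly. It asks whether the recommended treatment was completed, and a patient who did 48 h and then more has completed it. Compliance is also defined against what clinicians recommend, not against the randomised arm, so a group A patient advised to wear a stocking could also score as fully compliant.

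The per-protocol set is required alongside intention-to-treat because crossover is expected. If over-users in group A are not identified, both sets contain them and both are diluted in the same direction. Agreement between the two sets would then give no reassurance about this deviation. No analysis plan can repair this afterwards, because the wear would not have been recorded.

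**Working it through.** **1. The plan's own figure.** Inputs from Sample size and study duration: 98% occlusion in group B, margin -6 points, one-sided 2.5%, power 90%. With no true difference assumed and unpooled variance:

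n per arm = (1.960 + 1.282)² × 2 × 0.98 × 0.02 / 0.06² = 10.51 × 0.0392 / 0.0036 = 114.4, rounded up to 115, or 230 in total. The stated minimum is reproduced. The planned 360 less 20% drop-out leaves 288, or 144 per arm, which is used below.

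**2. What the item can detect.**

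| Behaviour | Likely answer | Asked about actual wear? |
|---|---|---|
| A: bandage removed before 48 h | below entirely | yes |
| A: 48 h, then extra compression | can be entirely | not necessarily |
| B: stocking stopped early | below entirely | yes |

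Under-use is captured in both arms. Over-use in group A is captured only if the patient or the investigator counts it as not fully following the protocol.

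**3. Timing.** Group B's regimen lasts 24 h + 7 days = 8 days. A visit at 7 days from surgery falls about 1 day before it ends. The only later answer is at 3 months, by recall. Group A's 48 h is over well before the 1-week visit, so that visit could pick up extra wear on days 3 to 7 if it asked about it.

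**4. Illustration of size.** Assumptions: true occlusion is 92% in group A under its assigned regimen and 98% in group B, a deficit exactly at the margin. A share c of group A has undetected over-use and obtains group B's result. The documents do not give c, so a range is shown.

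- Observed rate in A: pA = 0.92 + 0.06c
- SE = √[pA(1 − pA)/144 + 0.98 × 0.02/144]
- Chance of falsely declaring non-inferiority = Φ(0.06c/SE − 1.96)

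| c | pA | SE | Normal approximation | Exact enumeration of the Wald test |
|---|---|---|---|---|
| 0 | 0.920 | 0.0254 | 2.5% | 3.5% |
| 5% | 0.923 | 0.0251 | 3.3% | 4.5% |
| 10% | 0.926 | 0.0247 | 4.3% | 5.8% |
| 20% | 0.932 | 0.0240 | 7.2% | 9.2% |
| 30% | 0.938 | 0.0232 | 11.8% | 14.2% |

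The exact column starts above 2.5% because the Wald test is itself somewhat liberal at these rates and this sample size. The rise with c is similar in both columns. Undetected over-users stay in the per-protocol set, so the bias applies to both sets.

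**The case against.** The strongest reply is that the trigger for the follow-up question is not fully following the study protocol, which is wider than not completing treatment. A group A patient who adds compression has, on a natural reading, not fully followed a 48 h regimen. The data-collection section also names deviation separately from discontinuation. This stands in part. A reader might infer that extra compression in group A is certain to go unseen, and the wording does not support that. It supports a risk: the only question described is about completion, and the next one depends on the answer.

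A reader might also infer that the per-protocol set cannot protect the conclusion at all. That is not shown either. Under-use and admitted deviations are recorded, both sets must agree, and the definition of the per-protocol set may be in the full protocol, which is not shown. The absence of that definition from the article is not the complaint.

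The timing point should not be pressed. It concerns about the last day of group B's stocking, it assumes a visit at exactly 7 days from surgery, and compliance is asked again at 3 months. What remains is an early answer that cannot confirm completion and a late one that relies on memory.

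On size, the article dwells on stockings being uncomfortable and poorly tolerated. That points to under-use in group B, which the item does capture, more than to heavy over-use in group A. No single over-use rate should therefore be presented as likely. Finally, excluding over-users selects on behaviour after randomisation. If they added compression because of symptoms, the per-protocol comparison can be biased by their removal. This is a reason to record wear for everyone and keep the intention-to-treat result alongside, not a reason to leave wear unrecorded.

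**Conclusion.** The point holds as a risk in data collection. The compliance item measures completion and asks about actual wear conditionally, so extra compression in group A may be missed and retained in both sets on which the conclusion depends. The direction of the bias, towards non-inferiority, follows if extra compression moves group A's result towards group B's. Its size is unknown. For 5% to 30% undetected over-use, the false non-inferiority rate at the margin rises from 2.5% to between about 3.3% and 11.8% by the normal approximation. Those figures rest on a true deficit exactly at -6 points, over-users obtaining group B's full result, none of them being detected, and 144 evaluable patients per arm. With a smaller true deficit or partial detection the harm is less. The early timing of the 1-week answer is secondary.

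**What to change.** Ask every patient in both arms, whatever the compliance score, two things: what type of compression they wore, and the date they last wore it. Take the answers at a contact that covers the whole of group B's 24 h plus 1 week regimen. This can be the visit itself or the phone or WeChat contact that the article already provides for. Use these data when deciding per-protocol membership, and set the rule without sight of outcomes.

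Recruitment was expected to finish on 31 August 2023, before the article appeared on 12 October 2023, so some or all patients may be past the early contact. For them, ask at the 3-month visit.

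The cost is two extra questions and, for some patients, one short call. Patients asked late will recall less accurately. No treatment, primary endpoint or sample size changes.
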